### Randomization and allocation concealment

#### Randomization

Randomized sequences will be generated by the Medical Research Design and Data Processing Center of Xinjiang Medical University Affiliated Hospital of Traditional Chinese Medicine as the third party. SPSS 19.0 (SPSS Inc., Chicago, Illinois, United States) software (seed = 20,000) will be used to generate serial numbers for the subjects; 100 random numbers and the allocation sequence table of the randomized group will be preserved as blind codes. Subjects will be assigned to the experimental (n = 50) and control groups (n = 50) at a ratio of 1:1.

### Allocation concealment

Based on the randomized sequences, the third party will place paper strips with black characters on a grey background into non-transparent envelopes which are sealed with adhesive.

### Implementation

The randomized sequences will be generated by the third party. The researchers consist of personnel from the Department of Ophthalmology at the Xinjiang Uygur Autonomous Region Institute of Traditional Chinese Medicine. The subjects will be allocated into experimental and control groups by researchers according to the randomized sequences generated. One copy of the blind codes containing the random serial numbers will be preserved by the third party and research director. The physician responsible for determining the primary and secondary outcomes will be blind to the grouping of subjects and will not participate in the acupuncture treatment. All outcomes will be assessed and the results will be analyzed by a statistician blinded with respect to the allocations of the different treatments.

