## Trial status

The first participant was included on 27 November 2013 and to date, six participants have been recruited. The study will be finished on 30 June 2015.

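### Sealed envelopes are planned, but the research director also keeps the allocation codes and the Implementation section does not tie assignment to the envelopes: an avoidable weakness in concealment

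*Protocol article*

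**What the plan says.** Four sections of the protocol article bear on this.

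- **Randomization.** A data center of the same hospital, described as a third party, generates the list in SPSS 19.0: "software (seed = 20,000) will be used to generate serial numbers for the subjects". The same sentence continues: "100 random numbers and the allocation sequence table of the randomized group will be preserved as blind codes". The target is 50 children per arm.
- **Allocation concealment.** The third party puts paper strips into "non-transparent envelopes which are sealed with adhesive".
- **Implementation.** On custody of the codes: "One copy of the blind codes containing the random serial numbers will be preserved by the third party and research director". On who assigns: "The subjects will be allocated into experimental and control groups by researchers according to the randomized sequences generated". On who they are: "The researchers consist of personnel from the Department of Ophthalmology at the Xinjiang Uygur Autonomous Region Institute of Traditional Chinese Medicine". This section does not mention the envelopes.
- **Trial status.** At writing, "to date, six participants have been recruited".

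Two further places give context. Recruitment sets the study in that same ophthalmology department and has children enter after an eye examination. The Discussion says that no sham acupuncture arm will be used.

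**The concern.** Concealment works only if nobody involved in enrolment can learn the next assignment before a child is entered. Sealed opaque envelopes serve that purpose. A second copy of the list with the study's lead works against it, and so does a sentence that can be read as staff working from the list.

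A study lead might need the codes to break a blind in an emergency. Here the arm is visible to the child, the guardian and the acupuncturist, so that need is not evident. The copy adds risk for no stated benefit.

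What is at stake is selection at entry. A person who knows the next assignment can influence which child is enrolled next, or when. The safeguards named in Implementation, a blinded outcome physician and a blinded statistician, act after assignment. They protect measurement and analysis but cannot restore comparability lost at entry.

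**Working it through.** The main check is a comparison of text. Arithmetic is needed only for the count of open assignments and for scale.

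**1. Setting the sections side by side**

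| Question | Randomization / Allocation concealment | Implementation |
|---|---|---|
| Who makes the list? | Third-party center | Third party |
| Who keeps the codes? | Kept as blind codes, no holder named | Third party and research director |
| What carries the assignment to the child? | Opaque sealed envelopes | Researchers, following the sequences; envelopes not mentioned |
| Is the director kept out of enrolment? | Not stated | Not stated |

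The Randomization section defines the blind codes to include the allocation table. The director's copy is therefore described as a copy of the blind codes, whose contents are the assignments themselves and not only a set of subject numbers.

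The sentence on who allocates has two readings. Staff may open envelopes that carry the sequence, which is acceptable, or they may consult the sequence directly, which is not. The text does not decide between them. The director's copy is a weakness under either reading.

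**2. Assignments open at writing**

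100 planned − 6 recruited = 94. This is the count when the article was written. The count when readers could first see the seed is not given and could be anything from 94 down to 0.

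**3. Does the printed seed disclose the list?**

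Printed: the software and version, the seed, 100 numbers and the 50:50 split. Not printed: the SPSS procedure, the random-number generator, and the rule that turns numbers into arms, including whether blocks are used. The list cannot be shown to be recoverable from what is printed. It might be recovered by someone who guessed the rest correctly.

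**4. Scale, by illustration only**

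Let f be the fraction of each arm whose entry was steered, and g the difference in prognosis between steered children in the two arms. With no treatment effect, the expected difference between arms is

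shift = f × g.

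Both f and g are assumptions. For g, I take one combined SD from the Sample size section, 0.25 D.

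- f = 5%: 0.05 × 0.25 = 0.0125 D
- f = 20%: 0.20 × 0.25 = 0.05 D

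There are two yardsticks. The first is the 0.2 D boundary in Sample size, of which these shifts are 0.0125/0.2 = 6% and 0.05/0.2 = 25%. The second is the smallest difference from zero that would be significant one-sided at 0.05. With 20% dropout, 100 × 0.80 = 80 children remain, or 40 per arm, and the threshold is 1.665 × 0.25 × √(2/40) = 0.093 D. The shifts are 0.0125/0.093 = 13% and 0.05/0.093 = 54% of it.

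**The case against.** The strongest reply is that a proper concealment method is specified. A third party prepares opaque sealed envelopes, and the ordinary meaning of allocating by the sequences is that site staff apply whatever the envelope contains. Someone at the site has to do so. The director is said only to preserve a copy, not to screen, consent or enrol, and the copy may itself be sealed. A condensed article need not spell out numbering and opening rules, and outcome examiners are kept apart from treatment.

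Much of this stands. A reader might infer that concealment is not secured, or that researchers hold the list. The documents support neither: the envelopes are there, and nothing says that enrolling staff see the list. A reader might also infer that the printed seed exposes 94 assignments. That is unsupported too, because the procedure and assignment rule are not given and 94 is the count at writing only. Nor is open-label the article's own term. Treatment is known to participants and the acupuncturist, while assessors and the statistician are blinded.

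The reply does not remove the stated custody rule. The article says that the director keeps the codes, gives no purpose for it, and does not keep the director apart from enrolment. That is an explicit provision, not detail left to a longer document.

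**Conclusion.** The point holds in a limited form. Concealment is planned adequately in the Allocation concealment section and weakened in Implementation by the director's copy and by wording that bypasses the envelopes. The fault is unnecessary access and an unreconciled description, not demonstrated foreknowledge or misuse.

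Its size cannot be estimated from the article. The illustration of about 0.01 to 0.05 D rests wholly on an assumed steering rate of 5% to 20% and an assumed gap of 0.25 D, so it shows scale and is not evidence of bias. At the upper end, the shift would be large enough to matter beside the trial's 0.2 D boundary. The printed seed is a secondary, precautionary matter. The correction should be made because it is cheap and because little of the sample had been assigned at writing.

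**What to change.** 1. **Custody.** In Implementation, state that the Medical Research Design and Data Processing Center alone holds the list until database lock, and withdraw the research director's copy.
2. **Assignment.** Reword the sentence on who allocates so that a child is assigned only by opening the next of the envelopes described under Allocation concealment, after consent and baseline data are recorded.
3. **Seed (precaution).** Have the center regenerate whatever part of the list is still unused, with a seed that is not published. To keep 50:50 totals, if a of the first six children went to acupuncture, the remaining 94 places are 50 − a acupuncture and 44 + a control.

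The first two items change two sentences. The third needs one new run by the existing center and a fresh set of envelopes. The change should be notified by the route in the Protocol amendments section if the team treats it as a major modification. The director loses direct access to the codes, which matters little because the arm is already visible to those giving and receiving treatment. Treatment, visits and sample size are unaffected.

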### Intervention

Subjects in the acupuncture group will wear SVLs. Acupuncture will be performed at five acupuncture points (bilateral Cuanzhu (BL2), Tongziliao (GB1), Sibai (ST2), Muchuang (GB16), and Hegu (LI4), see Figures 
2 and
3). Alcohol (75%) will be used to routinely disinfect the local skin at the acupuncture points and 0.25 mm × 0.4 mm disposable sterile acupuncture needles (Suzhou Acupuncture & Moxibustion Appliance Co., Ltd., Suzhou, China) will be used at acupuncture points Sibai and Hegu to a depth of 0.5 to 1.0 cm. After achieving *de-qi* (Subjects have a feeling of soreness, fullness, aching, heaviness at and around the acupoints), the needle will be held in position for 20 minutes. Cuanzhu will be acupunctured to a depth of 0.3 to 0.5 cm. Tongziliao and Muchuang will be acupunctured to a depth of 0.1 to 0.3 cm. After achieving *de-qi*, the needle will be held in position for 20 minutes. Acupuncture will be carried out once a day between 10:00 and 19:00 (Beijing time). One cycle of treatment will last for nine days, followed by one day of no treatment. Six cycles of treatment will be undertaken continuously for a total of 60 days. The acupuncturist in this study, a physician with 18 years of experience in clinical acupuncture, will not participate in objective examinations, such as visual acuity. Subjects in the control group will wear SVLs without any other treatment affecting visual acuity. Observations will be carried out for two consecutive months.

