**Methods/Design:**

A randomized, parallel, single-center, assessor- and statistician-blinded, controlled clinical trial will be performed. A total of 100 teenagers, between seven and 12 years of age, with mild-to-moderate myopia and spherical lenses <-6.00 D and cylindrical lenses <-1.50 D will be selected from the Xinjiang Uygur Autonomous Region Institute of Traditional Chinese Medicine, a grade III level A teaching hospital in Urumqi, Xinjiang, China (Xinjiang Medical University Affiliated Hospital of Traditional Medicine). The subjects will be randomly assigned to two different groups (control and acupuncture groups), each group containing 50 subjects. The subjects in both groups wear single-vision corrective lenses. In the acupuncture group, acupuncture will be performed daily for nine consecutive days on five points (bilateral Cuanzhu, Tongziliao, Sibai, Muchuang, and Hegu), followed by no treatment for one day. Six cycles of treatment will be undertaken continuously for a total of 60 days. Following 60 days of treatment, a follow-up period of six months will be included. The primary outcome will be diopter determination. The secondary outcomes will include distance visual acuity, axial length, lens thickness, ciliary body thickness, and subjective symptoms of the eyes and entire body. The main time points for the evaluation of clinical efficacy will be the first, third, and sixth months after treatment.

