**Table 1 Tab1:** **Time of visit and data collection**

Data obtained/recorded	Baseline	Treatment phase	Visit 1	Visit 2	Visit 3
	-7 days	1-2 months	3 months	5 months	8 months
Signed informed consent	×				
Medical history	×				
Met the diagnostic standard/exclusion criteria	×				
General record	×				
Diagnosis	×				
Visual acuity	×		×	×	×
Diopter	×		×	×	×
Axial length	×		×	×	×
Lens thickness	×		×	×	×
Ciliary body thickness	×		×	×	×
Skin damage	×	×	×	×	×
Eye symptoms and systemic symptoms	×	×	×	×	×
Randomization	×				
Group therapy	×				
Case report form	×		×	×	×
Adverse event		×	×	×	×
Close-out					×

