### Recruitment strategies

The subjects will be informed of the details regarding the trial plan and those who voluntarily participate in the trial will receive free ophthalmologic examinations. Following optometric evaluation, these subjects will receive the highest discount (30% off) on glasses. Subjects in the experimental group will receive a 50% discount on acupuncture treatment. All subjects who receive a follow-up eye exam will not pay a fee and will be permitted to be fast-tracked. The subjects who will be included in the experimental group will receive treatment any time between 10:00 and 19:00 (Beijing time). If adverse events occur during treatment, the treatment will be immediately terminated, and help will be obtained from the emergency department. According to the specific condition which occurs after treatment, a consultation involving at least three experts will be carried out to decide whether or not to continue the clinical trial. Subject compliance will be determined based on whether or not the subject receives due treatment. The researchers will ensure that the subjects in the experimental group fully understand the importance of regular acupuncture and compliance. During the observation period, the use of drugs or other therapies to treat mild-to-moderate myopia will be prohibited.

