**Table 2 Tab2:** **Variables, measures, and methods of analysis**

Variable/outcome	Hypothesis	Outcome measure	Methods of analysis
1) Primary	Intervention improved outcome from baseline to 7 days	Adherence% (>80%) [binary]	
Diopter	Diopter reduced or increased after treatment	Diopter [continuous]	t-test (rank-sum test) or repeated measurement
2) Secondary	Intervention improved outcome from baseline to 7 days	Adherence% (>80%) [binary]	
Visual acuity	Visual acuity did not increase or decrease after treatment	Visual acuity changes [continuous]	t-test (rank-sum test) or repeated measurement
Axial length	Axial length was not increased	Axial length changes [continuous]	t-test (rank-sum test) or repeated measurement
Lens thickness	Lens thickness was not increased	Lens thickness changes [continuous]	t-test (rank-sum test) or repeated measurement
Ciliary body thickness	Ciliary body thickness was not increased	Ciliary body thickness changes [continuous]	t-test (rank-sum test) or repeated measurement
Eye symptoms and systemic symptoms	No adverse symptoms	No adverse symptoms	Chi-squared test or Fisher’s exact test
Compliance	Compliance	Cure rate [binary]	Chi-squared test or Fisher’s exact test
Combination therapy/treatment	Improvement occurred	Whether other drugs were used during treatment [binary]	Chi-squared test or Fisher’s exact test
Adverse event	Improvement occurred	Presence of drug-related adverse event [binary]	Chi-squared test or Fisher’s exact test
3) Baseline analyses:		Adherence% (>80%) [continuous]	
Age		CRF [continuous]	t-test (rank-sum test)
Weight and height		CRF [continuous]	t-test (rank-sum test)
Female versus male		CRF [binary]	Chi-squared test or Fisher’s exact test
Race		CRF [more categories]	Chi-squared test or rank-sum test
Birth weight		CRF [continuous]	t-test (rank-sum test)
Preterm children		CRF [binary]	Chi-squared test or Fisher’s exact test
Parental myopia or not		CRF [binary]	Chi-squared test or Fisher’s exact test
Sibling myopia or not		CRF [binary]	Chi-squared test or Fisher’s exact test
Daily close reading time		CRF [continuous]	t-test (rank-sum test)
Outdoor time		CRF [continuous]	t-test (rank-sum test)
Eye exercises every day or not		CRF [binary]	Chi-squared test or Fisher’s exact test
Daily sleep time		CRF [continuous]	t-test (rank-sum test)
Room light conditions		CRF [binary]	Chi-squared test or Fisher’s exact test
Poor reading habits		CRF [more categories]	Chi-squared test or rank-sum test

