The limitations of the proposed study are three-fold. Firstly, due to a limited budget, the proposed study will not be a multicenter trial, which will influence the external validity of the conclusions. Secondly, common fake acupuncture methods include neighboring sham acupuncture, non-specific site acupuncture, superficial acupuncture, minimal acupuncture, and a placebo needle; all of these methods could be used as a control, but with obvious deficiencies
[33]. Therefore, in the proposed study a sham acupuncture group will not be included. Quantitative, objective indices, such as diopter, AL, lens thickness, and ciliary body thickness will be selected as the outcomes to evaluate the clinical efficacy at a reduced bias. Thirdly, in the proposed study, 100 cases will be included and followed up on for six months. To prevent bias caused by loss-to-follow-up, the following measures will be adopted: first, the subjects will be from an elementary school near the hospital. Second, before the subjects are entered into the proposed study, their guardians will fully understood the specific requirements of the follow-up schedule, as outlined in the informed consent form. Once the subjects are included in the study, communication with the guardians will be strengthened by phone calls or email. The subjects will be informed of the follow-up examination time and place in advance. The subjects will receive the follow-up examination immediately after arriving.

This will be a randomized, parallel controlled trial, and it is anticipated that acupuncture treatment of adolescent mild-to-moderate myopia will be shown to be safe and effective. The proposed study will demonstrate the specificity of the meridians and acupuncture points and provide evidence-based medical evidence on the use of acupuncture to treat myopia.

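### The window for the ban on other myopia treatment is ambiguous, and the one stated measure of such treatment misses non-drug therapy and all of the follow-up in which efficacy is measured

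*Protocol article*

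**What the plan says.** Four places in the protocol article bear on this point.

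- **Ban on other treatment (Recruitment strategies):** "During the observation period, the use of drugs or other therapies to treat mild-to-moderate myopia will be prohibited". No start, end or length is given there, and the term is not defined elsewhere.
- **Length of observation (Intervention):** directly after "Subjects in the control group will wear SVLs without any other treatment affecting visual acuity", the section ends with "Observations will be carried out for two consecutive months". The acupuncture course in the same section has the same length: "Six cycles of treatment will be undertaken continuously for a total of 60 days".
- **Length of follow-up:** the abstract's Methods/Design says "Following 60 days of treatment, a follow-up period of six months will be included", and the Discussion repeats that "100 cases will be included and followed up on for six months". The column heads of Table 1 agree: "7 days 1-2 months 3 months 5 months 8 months". Table 1 places refraction, acuity, axial length, and the lens and ciliary body measurements at baseline and the last three columns only, with none in the treatment phase.
- **Measure of other treatment (Table 2):** the row on combination therapy has the outcome measure "Whether other drugs were used during treatment [binary". Table 1 has no row for concomitant treatment.

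The Harms section also uses the term observation period, for adverse events. Table 1 collects these from the treatment phase to month 8.

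**The concern.** Two things do not fit together. First, the term that sets the duration of the ban can be read as two months (Intervention) or as about eight (Harms with Table 1, and the stated follow-up). Sites and families cannot tell from the text which applies. Second, the ban covers drugs and other therapies, but the measure in Table 2 covers drugs alone, and only during treatment.

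This matters because of the design. Only the assessors and the statistician are blinded, there is no sham arm, and the abstract itself describes acupuncture for myopia as common practice in China. A family allocated to spectacles alone knows it and may seek treatment elsewhere. Families in the acupuncture arm may also add treatment once the 60 days are over. Either would change the between-arm difference at the visits on which efficacy is judged. The Statistical analysis section names both a full analysis set and a per-protocol set. The second cannot reflect adherence to the ban if breaches of most of it are not asked about.

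**Working it through.** **Timeline.** Treatment is 6 cycles × (9 + 1) days = 60 days, or two months. The Primary outcome section evaluates at one, three and six months after that: 2 + 1 = 3, 2 + 3 = 5, 2 + 6 = 8. This reproduces the visit months in Table 1.

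**Distance from the end of the ban to each efficacy visit.**

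| Reading of the observation period | Month 3 | Month 5 | Month 8 |
|---|---|---|---|
| Two months (Intervention) | 1 month after the ban ends | 3 months after | 6 months after |
| To the last visit (Harms with Table 1) | within the ban | within the ban | within the ban |

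**What the ban covers against what Table 2 measures.**

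| Type and time of other treatment | Banned, two-month reading | Banned, eight-month reading | In the Table 2 measure |
|---|---|---|---|
| Drugs, months 1-2 | yes | yes | yes |
| Non-drug therapy, months 1-2 | yes | yes | no |
| Drugs, months 3-8 | unclear | yes | no |
| Non-drug therapy, months 3-8 | unclear | yes | no |

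The two cells marked unclear arise because the restriction on controls in the Intervention section has no end date of its own. The measure fills one cell of four under either reading. It covers drug use in 2 of 8 months, leaving 8 − 2 = 6 months uncovered, and non-drug therapy in 0 of 8.

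**Possible dilution (illustration only).** The documents give no crossover rate. Let c be the fraction of control children who obtain acupuncture elsewhere, and f the share of its benefit that they gain. The expected difference is then the true difference × (1 − c × f). With f = 1, the worst case:

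- c = 10%: 1 − 0.10 = 90% of the true difference remains
- c = 20%: 1 − 0.20 = 80%
- c = one third: 1 − 1/3 = 67%

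With f = 0 nothing is lost, so at c = 20% the range is 80% to 100%. I do not convert this to diopters or power. That would need an effect size, and the point does not depend on one.

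**The case against.** A reader might infer something stronger: that the ban lapses at two months, that controls may then cross over before any outcome is taken, and that nothing would record it. The documents do not support this.

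- **Two months is not the only duration given.** The abstract, the Discussion and Table 1 all give six further months. The two-month sentence may mean only that controls are observed in parallel with the treatment phase.
- **The ban does not cite the two months.** The other use of the same term, in Harms, fits a period to month 8.
- **Other restrictions have no time limit.** The spectacles-only rule for controls has no end date of its own, and neither does the withdrawal condition on prohibited Chinese or Western drugs. No passage permits crossover.
- **Not every outcome comes after month 2.** Eye and systemic symptoms, a secondary outcome, are also recorded in the treatment phase.
- **Some recording exists.** Drug use during treatment is a Table 2 variable, a violation of the plan that leads to dropout must be explained in the case report form, and the full form is not shown.
- **Dilution would not be uniform.** A control child who began a 60-day course at the end of month 2 would finish at month 4, after the month-3 visit.

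All of this stands, and it limits the point to what is claimed here. It does not remove it. That the term can plausibly mean eight months shows that the text needs reconciling. The withdrawal condition speaks of medicine and drugs and does not name acupuncture or other non-drug therapy. The dropout rule catches only breaches that come to light and end participation. The missing form could hold more, but the criticism is of the measure that Table 2 does state, which is narrower than the ban.

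**Conclusion.** The concern holds in this limited form. The window of the ban is ambiguous between two months and about eight. Separately, and under either reading, the stated measure of other treatment omits non-drug therapy throughout and everything started in months 3 to 8. All three post-baseline assessments of the primary outcome, and of acuity and biometry, fall in those months.

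The consequence is one of interpretation. A diluted or null result could not be told apart from contamination, and the per-protocol analysis could not be aligned with the plan's own rule. Whether this would change the result depends on a crossover rate that the documents do not give; the percentages above are assumptions. The conclusion rests on Table 2 as printed and on families knowing their allocation, which follows from the absence of a sham.

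**What to change.** 1. Reconcile Recruitment strategies, Intervention, Harms and Table 1 so that one observation window, the same for both arms, is defined with a start and an end, and let the rule on other treatment refer to it. Which window and which rule apply is for the sponsor to decide.
2. Replace the Table 2 measure with: any other myopia treatment (drug, acupuncture outside the allocated course, or other therapy) from randomisation to the month-8 visit. Add a matching row to Table 1.
3. Ask the question in both arms at visits 1, 2 and 3, with type and start date.
4. Keep the intention-to-treat analysis already stated, and report such use by arm beside the full-analysis-set and per-protocol results.

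The cost is some protocol wording, one more question at visits that already take place, and the possibility that crossover has to be reported. Trial status gives six participants recruited at the time of writing, so at that point nearly all of the information could still be collected.
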